**Methods:**

A total of 100 patients with previous reconstructive knee surgery and 20 healthy controls will be examined twice at a 9-month interval for both knees. Acoustic emissions (AE) will be recorded with the Inmodi knee brace (École Polytechnique Fédérale de Lausanne; EPFL) during 4 functional tests (unloaded flexion-extension, sit-to-stand test, one-step test, and walk test). Gold-standard osteoarthritis diagnostics will be assessed and evaluated by an experienced radiologist for (1) the magnetic resonance imaging (MRI) Osteoarthritis Knee Score (MOAKS) and (2) the Kellgren-Lawrence (KL) grading scores. Feature analysis and multivariate modeling will be used to study the association between the extracted sound parameters and osteoarthritis (MOAKS and KL). In addition, thermal images will be taken to investigate the state of inflammation. Participants will fill out 5 health-related questionnaires (Oxford Knee Score [OKS], Core Outcome Measures Index [COMI], University of California at Los Angeles [UCLA ]activity scale, Knee Injury and Osteoarthritis Outcome Score [KOOS], and Forgotten Joint Knee Score-12 [FJS-12]) at both time points.

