### Project Population

This study targets a population at risk of osteoarthritis. The risk of knee osteoarthritis after knee joint injury is up to 5-fold that of noninjured patients. As many as 50% of individuals with an anterior cruciate ligament (ACL) or meniscus tear develop knee osteoarthritis [21]. Therefore, to represent the whole distribution of osteoarthritis stages in the study sample, participants will be recruited from the clinic’s Meniscus/ACL/Cartilage (MAC) surgery registry at 2- and 5-year postoperative times. All patients from the MAC registry will be screened regardless of whether they have undergone isolated meniscal tear repair, isolated ligament reconstruction, or a combined meniscal and ligament procedure. Additionally, a healthy control group and a late-stage osteoarthritis group will also be included. The inclusion and exclusion criteria presented in Textbox 1, follow established standards and are consistent with those used in similar studies (eg, NCT02937064).

The total study sample will be 120 patients in 6 groups:

Group A: 20 healthy participantsGroup B1: 20 patients from the MAC registry at 2 years postoperative with normal outcomes (normal and poor outcomes are defined in section Recruitment)Group B2: 20 patients from the MAC registry at 2 years postoperative with poor outcomesGroup C1: 20 patients from the MAC registry at 5 years postoperative with normal outcomesGroup C2: 20 patients from the MAC registry at 5 years postoperative with poor outcomesGroup D: 20 patients booked for in-house unilateral TKA surgery for severe osteoarthritis

Even if it is not possible to perform an exact power analysis for the ML models to be trained, we can use a simple proxy model to estimate the effect size that we can reasonably expect to detect with a sample size of 120. Thus, if we aim to estimate the differences in KL gradings from the AEs, the smallest detectable correlation with 80% power and a significance level of *P*=.05 would be 0.25. In one-way ANOVA, this corresponds to a minimum explained variance of approximately 7%, which is considered a small-to-medium effect size [22]. Smaller effect sizes are unlikely to be detected within our population.

Textbox 1.Detailed inclusion and exclusion criteria for the groups.

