Unloaded flexion-extension (F-E) of the knee in a seated position, starting with a knee angle of 90°, followed by a full extension and returning to the starting position (6 times). A video will guide the pace of the motion to normalize the velocity among patients (comfortable speed).Sit-to-stand test (STS) at a comfortable pace (6 times). Force plates (FP-BTA; Vernier) will be used during this exercise to assess the ground reaction force for each sole and detect any asymmetrical loading of the joints.One-step test (OST) is an exercise step platform, which will be used to perform a complete ascent and descent at a comfortable speed (6 times per leg).Walk test at a comfortable pace (10m ×2 times).

The following measurements will be performed together with the AE tests:

Temperature assessment: thermal distribution of the knee joint will be assessed with a far infrared thermal sensor array (MLX90640; Melexis) to evaluate the state of inflammation. Localized thermal images will be recorded at three time points: (1) at the beginning of the whole test, just after arriving, (2) after warming up (5 minutes on a stationary bicycle), and (3) at the end of all tests.Pain assessment: after the test session, the level of knee pain will be assessed using a visual analog scale. Participants will quantify the maximum knee pain experienced during the tests for each knee separately by placing a vertical mark on a 10 cm horizontal line. The line ranges from 0 (“no pain at all”) to 10 (“not endurable pain”).

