#### PROMs

The following PROMs questionnaires were sent out by email or paper form depending on participants’ preference and were completed in their homes.

Oxford Knee Score (OKS): this instrument contains 12 questions about an individual’s activities of daily living and how they have been affected by pain over the last 4 weeks. Its summed score ranges from 0 (severe functional problems) to 48 (excellent knee function) [30,31].Core Outcome Measures Index (COMI) knee: assesses the main outcomes of importance to patients with knee problems (pain, function, symptom-specific well-being, quality of life, disability). It is a 6-item multidimensional instrument with 5 domain scores for pain (item 1), function (item 2), symptom-specific well-being (item 3), general quality of life (item 4), and disability (average of items 5 and 6) are averaged to give a COMI score ranging from 0 to 10 (the higher the score, the worse the status) [32].University of California at Los Angeles (UCLA): an activity rating scale, which rates the activity level of joint replacement patients globally from 1 to 10. The patient indicates her/his most appropriate activity level (level 1 = “no physical activity, dependent on others”; level 10 = “regular participation in impact sports”) [33].Knee Injury and Osteoarthritis Outcome Score (KOOS): an instrument to assess the patient’s opinion about their knee and associated problems. There are 5 subscales with individual sum scores normalized to 0-100 (0 = “extreme symptoms”; 100 = “no symptoms”): pain, other symptoms, function in daily living, function in sport and recreation, and knee-related quality of life. A total score of all subscales combined has not been validated [34].Forgotten Joint Score 12 (FJS-12) is a concise 12-item PROM that evaluates patients’ ability to forget their joints daily. Each item is answered within a 5-point Likert scale with the following response options: never (0); almost never (1); seldom (2); sometimes (3); and mostly (4) [35].

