### Feature Analysis and Multivariate Modeling

In this stage we will study the association between the extracted parameters and osteoarthritis (using the KL or MOAKS grading as the dependent variable), both individually for each feature and also by creating linear and nonlinear multivariate models. For this, we will follow a strategy guided by the principles of (1) increasing complexity and (2) clinical explainability. Thus, the initial models we consider are linear discriminant analysis and logistic regression, which would be ideal options in case we have a reduced number of highly informative and discriminative features. In this ideal scenario, the models would be highly interpretable and easily translatable to a clinical description. In case more sophisticated models are required, we prioritize ensembles of decision trees, such as random forest and gradient boosting, due to the possibility of performing advanced feature importance analysis and derivation of statistical decision rules.

All features will be tested for normality by Shapiro-Wilk tests and presented as mean (SD; normally distributed data) or median and range and, if needed, in histograms, box plots, or violin plots (nonnormal data).

Associations between AE parameters and osteoarthritis (KL or MOAKS grading) will be evaluated using Pearson (normally distributed data) or Spearman (nonnormal data) repeated measures correlation coefficients, as well as with logistic regression models. Mixed ANOVA will be used to compare differences in the AE, osteoarthritis grading parameters between groups. Also, we will specifically assess the relevance of potential confounding variables such as BMI, age, activity level, and gender. The significance level will be set to *P*=.05, and due to the potentially large number of tests, we will apply the Holm post-hoc correction to all *P* values. For multivariate models, the statistical association will be characterized using leave-one-subject-out nested cross-validation, with a subsequent estimation of a confidence interval for prediction accuracy. This is the most conservative and robust cross-validation strategy for overfitting , and with our sample size (n=120), we will have a good estimation of the model variance. Statistical analyses will be done with R (version 4; R Foundation), Matlab (version 2021b or higher; MathWorks, Inc), and Python (version 3.6 or higher; Python Software Foundation).

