## Discussion

### Principal Findings

This exploratory study aims to identify biomarkers with a prognostic value in the prediction of osteoarthritis. Acoustic, kinematic, and thermal features will be extracted and combined with an artificial intelligence algorithm, and evaluated against gold-standard osteoarthritis diagnosis, such as radiographs and MRI. Some candidate acoustic biomarkers have been identified in a preliminary study [9], using a multifractal analysis method. However, multiple other candidates will be evaluated individually or in combination in our study. Therefore, the primary endpoint can be defined as the area under the curve of the receiver operating characteristic analysis of each biomarker or combination of biomarkers in the regression analysis, finally identifying the parameters with the highest sensitivity and specificity to predict early-stage osteoarthritis in clinical use. AE is patient-dependent, and as such, demographic and baseline health data will be captured and entered as covariates in the regression models. The secondary objective is to evaluate the value of these biomarkers in predicting osteoarthritis evolution. For this objective, the patients will be examined a second time at 9-month intervals, and the new biomarkers will be introduced in regression models to evaluate the predicted performance for osteoarthritis evolution.

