Another concern is that resulting acoustic biomarkers may mostly reflect movement patterns rather than a causal relation to osteoarthritis. This critical aspect has been carefully considered in the design of the experimental protocol. As described in the study procedures section, the exercises (movements) the participants must perform are extremely standardized. Also, we will have the kinematic data associated with any potentially discriminative AEs. This allows us to study any movement patterns that may be associated with acoustic biomarkers and assess how strongly they are correlated with specific movements that may not be specific for osteoarthritis. Also, on top of the IMU in the device, sit-to-stand is performed on force plates, so an imbalanced load could also be accounted for in the models. On the other hand, we believe that finding movement patterns that are strongly correlated with the osteoarthritis gradings would be a very relevant contribution of the study, even if causal links cannot be directly established.

Finally, another limitation is the lack of medical history. Although patients are screened and asked about revision or previous surgeries as well as former injuries of the comparator knee, there is no guarantee a patient has not already been operated on or operated on again at a different hospital.

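### In groups B and C the between-knee contrast is also the surgical contrast, and the named covariates, all person-level, cannot separate surgical change from osteoarthritis

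*Protocol article*

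**What the plan says.** - **Design.** Each participant "will be examined twice at a 9-month interval for both knees" (Abstract, Methods). Groups B1, B2, C1 and C2 have 20 participants each. Textbox 1 requires them to have had surgery on one knee only and treats the other knee as an internal control. Under Project Population, registry patients are screened "regardless of whether they have undergone isolated meniscal tear repair, isolated ligament reconstruction, or a combined meniscal and ligament procedure".
- **Covariates.** Feature Analysis and Multivariate Modeling states "we will specifically assess the relevance of potential confounding variables such as BMI, age, activity level, and gender". Activity is measured by the UCLA scale, which "rates the activity level of joint replacement patients globally from 1 to 10" (PROMs), so there is one value per person. Principal Findings, having noted that acoustic emission depends on the patient, adds that "demographic and baseline health data will be captured and entered as covariates in the regression models". Operated knee and procedure type are not named as a covariate or stratum anywhere.
- **Surgery.** Limitations mentions recruitment after surgery only as a limit on generalization.
- **Movement.** Limitations raises the possibility that biomarkers reflect movement patterns, and answers that "the exercises (movements) the participants must perform are extremely standardized" and that kinematic data will show how far biomarkers track movement. In the section on the AE test, flexion-extension is paced: "A video will guide the pace of the motion to normalize the velocity among patients (comfortable speed". The next test reads "Sit-to-stand test (STS) at a comfortable pace (6 times", and the one-step and walk tests are likewise at the participant's own comfortable speed.

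**The concern.** Project Population chooses registry patients because knee injury raises osteoarthritis risk (up to 5-fold, with as many as 50% affected after a ligament or meniscus tear). In groups B and C the operated knee is therefore expected to have both the higher grade and the surgical change. If surgery itself alters knee sound, a feature can track KL or MOAKS grade without responding to osteoarthritis. BMI, age, activity and sex do not vary between a person's knees, so adjusting for them leaves this within-person association untouched.

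At stake is what the biomarker means. The stated aim is early-stage detection, and groups B and C were recruited as the at-risk population for it. A marker that partly reads surgical history may do less well in never-operated knees.

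Movement is a smaller matter: the safeguard in Limitations is worded more strongly than the test descriptions allow.

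**Working it through.** **Yardstick from the plan.** Project Population gives 0.25 as the smallest detectable correlation (N = 120, 80% power, significance level .05). Two-sided Fisher z gives tanh((1.960 + 0.842)/√117) = tanh(0.259) = 0.253. The figure reproduces.

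**Step 1: knees.** Groups B and C have 4 × 20 = 80 participants, so 80 operated and 80 comparator knees.

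**Step 2: separation of operated from unoperated knees.** Assume a normal feature, equal SDs and a 0.5 SD shift from surgery alone. AUC = Φ(0.5/√2) = 0.638. This is not yet an osteoarthritis AUC.

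**Step 3: spurious osteoarthritis AUC.** The feature carries no osteoarthritis signal. Let p1 be the operated share among knees with osteoarthritis and p0 the operated share among knees without. Pairs with the same surgical status contribute 0.5, and discordant pairs 0.638 or 0.362, so

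AUC = 0.5 + 0.138 × (p1 − p0).

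Take osteoarthritis in 50% of operated knees (40 of 80), the article's upper figure, and an assumed share in comparator knees:

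| Comparator knees with osteoarthritis | p1 | p0 | AUC |
|---|---|---|---|
| 0% (0 of 80) | 40/40 = 1.000 | 40/120 = 0.333 | 0.59 |
| 10% (8 of 80) | 40/48 = 0.833 | 40/112 = 0.357 | 0.57 |
| 20% (16 of 80) | 40/56 = 0.714 | 40/104 = 0.385 | 0.55 |

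With the comparator share held fixed, fewer affected operated knees give smaller values.

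**Step 4: spurious correlation.** The plan includes repeated-measures correlation. The article does not say whether the repeats are knees, visits or both; the following applies if knees are included. Assume the feature and the grade are each shifted by δ SD in the operated knee and are otherwise unrelated, with within-person correlation between knees of 0.5. The within-person correlation is δ²/(δ² + 2(1 − 0.5)) = δ²/(1 + δ²). The correlation pooled over the 160 knees is 0.25δ²/(1 + 0.25δ²).

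| δ (assumed) | Within-person | Pooled |
|---|---|---|
| 0.5 | 0.20 | 0.06 |
| 0.8 | 0.39 | 0.14 |
| 1.0 | 0.50 | 0.20 |

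A simulation of 80 participants with two knees each gave within-person values of 0.204, 0.393 and 0.500. The two larger exceed 0.25; no pooled value does. The 0.25 refers to 120 independent observations, so it serves only as a yardstick.

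**Step 5: movement.** Of the four tests, one is paced by video and three are self-paced. Tasks and repetitions or distances are fixed in all four; speed is fixed in one.

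**The case against.** **The covariate list is open.** The four variables are given as examples, and an article may leave the full list to another document. The design already distinguishes operated from comparator knee, and the planned mixed ANOVA has a within-subject factor that could be the knee. A reader might infer that operated status is excluded from the analysis; the text does not say so. What stands against this objection is that every named example is at the wrong level for this threat, and that surgery is nowhere treated as a rival explanation although movement is.

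**Movement is not ignored.** A reader might infer that speed is left out. The documents do not support that: Principal Findings makes kinematic features inputs to the algorithm, and Limitations names the risk, plans a kinematic check and says force-plate load could be modelled. Slow movement may also be a consequence of osteoarthritis, so forced adjustment for speed could remove real diagnostic signal. This objection largely succeeds; only the wording about standardization remains.

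**The effect may be modest.** The 0.638 of step 2 could be mistaken for the bias in the study endpoint. It would equal that bias only if every operated knee and no comparator knee had osteoarthritis. Pooled correlations are small at a 0.5 SD shift.

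**Other groups dilute the link.** Textbox 1 does not select groups A and D on reconstructive surgery, so 160 of 240 knees are not the registry-operated knee. A reader might infer that the biomarker would fail in people without surgery; the documents support only that it may do worse. The dilution helps mainly at the two ends of the severity range, healthy and severe, rather than at the early stage that groups B and C are meant to represent.

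**Conclusion.** The concern holds for surgery. In 80 of 120 participants the between-knee contrast coincides with the surgical contrast, and person-level covariates cannot separate the two. Under an assumed 0.5 SD surgical shift, with osteoarthritis in 50% of operated and 0-20% of comparator knees, the spurious osteoarthritis AUC is about 0.55-0.59. The spurious within-person correlation is about 0.20 when feature and grade both shift by 0.5 SD and about 0.39 at 0.8 SD. The documents give no estimate of the effect of surgery on knee sound, so these figures show what is possible rather than what is expected.

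For movement, only a mismatch of wording holds: three of the four tests are self-paced. Neither point invalidates an openly exploratory study, but the first affects how any leading biomarker can be interpreted and should be settled in the analysis.

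**What to change.** 1. In Feature Analysis and Multivariate Modeling, name operated knee (yes/no) as a knee-level variable.
2. Report each leading biomarker's AUC with and without that variable.
3. Report AUC separately within operated and within unoperated knees. Describe procedure type within operated knees only, since it is undefined elsewhere.
4. Report the kinematic check described in Limitations as a sensitivity analysis beside the unadjusted result, not as forced adjustment.
5. Limit the statement on standardized movement to the video-paced flexion-extension test, and say that the sit-to-stand, one-step and walk tests are self-paced.

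**Cost.** No new measurements should be needed: the design identifies the operated side in groups B and C, procedure type should be obtainable from the registry, and the brace records kinematics. Intervals within strata will be wider. Adjusting for operated status may absorb some true osteoarthritis signal, because the operated knee is also the one at higher risk; this is why both versions should be shown. Unoperated can only mean not known to be operated, since Limitations concedes that surgery at another hospital cannot be ruled out.

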### Statistics

Since this is an exploratory study, the statistical data analysis will also be mostly exploratory, so multiple techniques and models will be assessed and compared. Overall, the analysis of acoustic signals includes signal segmentation and denoising, feature extraction, feature analysis, and multivariate modeling.

To ensure the reproducibility of the experimental results, we will provide open-source access to the exact feature sets and analysis code for the reported results.

### Withdrawal and Discontinuation

The patients can withdraw from the study at any point in time. In the declaration of consent, the patient agrees that the data already collected stays in the study. Patients who have knee surgery or a knee injury within the follow-up time or patients who become otherwise severely ill will not be invited for the second visit. In all cases above, the data will be encrypted and used for evaluation. If the enrollment phase is still ongoing, the withdrawn patient will be replaced with a person of the same sex, comparable age, and study group type (A, B1, B2, C1, C2, and D).

If a participant misses the first visit as well as a substitute appointment, the participant will be withdrawn and replaced. If a participant misses the second visit and substitute appointment, his data collected from the first visit will be used.

If a person becomes pregnant, the study will continue but without EOS radiography.

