## Methods

### Project Design

This is a prospective, single-center, exploratory study. A cross-sectional and a longitudinal dataset will be collected. A total of 120 participants will be recruited and examined twice at a 9-month interval at the Schulthess Klinik in Zurich (see Table 1 for the measurement procedure). The cross-sectional dataset stems from the first visit of the participants and serves for the identification of AE biomarkers for osteoarthritis. The longitudinal dataset combines the data from the first and second visits and tests whether the osteoarthritis changes can be assessed from the biomarkers. A secondary aim is to evaluate the ability of the AE biomarkers from the first visit to predict the condition’s progression as observed during the second visit.

**Table 1. T1:** Summary table with all project visits, including relevant procedures and timelines.

Study period	Information	Screening	1st visit	2nd visit
Time point	Precall (maximum 2 months)	0	0-2 months	9 months (±2 months)
Oral and written information	✓			
Written consent		✓		
Check inclusion/ exclusion criteria		✓		
Anthropometric and patient data			✓	✓
EOS radiography			✓	✓
MRI^a^			✓	✓
Acoustic emission test with Inmodi knee brace			✓	✓
PROMs^b^ (at home)			✓	✓

a MRI: magnetic resonance imaging.

b PROM: patient reported-outcome measurement.

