### Handling of Missing Data

Patients who fail to appear for the MRI, EOS, or AE test with the Inmodi knee brace will be invited again. After the second miss, they will be excluded (and replaced if the recruitment phase is still ongoing). Missing source data from MRI or EOS are not expected. In the case of missing readouts in the electronic case report form, the radiologist is asked to do the missing readout or to give reasons for the missing.

In case of unexpected data loss or data damage with the Inmodi brace data collection, the participant will be reinvited.

Concerning PROMs, a maximum of 2 missing items is allowed in OKS. They will be imputed with the mean of all other responses. In case of additional missing items, the patient will be contacted to clarify. For COMI and UCLA, missing data will not be imputed. The patient will be contacted for clarification. For KOOS: If more than 50% of subscale items are missing, the subscale score cannot be calculated. Otherwise, the sum of the items answered is normalized to 0‐100. For FJS-12, if more than 4 of the answers are missing, the total score cannot be calculated. With fewer items missing, these can be replaced by the mean of the items answered. Generally, if a patient makes more than one entry for a question, the worst applies.

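### Two visits are stated for all 120 participants, but the surgery rule takes Group D (booked for TKA) out of the second visit, so the longitudinal dataset is nearer 100

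*Protocol article*

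**What the plan says.** Project Design in the protocol article states: "A total of 120 participants will be recruited and examined twice at a 9-month interval". The abstract repeats this: "A total of 100 patients with previous reconstructive knee surgery and 20 healthy controls will be examined twice". Table 1 schedules radiography, MRI, the acoustic test and the questionnaires at the second visit and exempts no group.

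Project Population sets out the sample: "The total study sample will be 120 patients in 6 groups", with 20 in each. Group D is "20 patients booked for in-house unilateral TKA surgery for severe osteoarthritis". Textbox 1 makes the booked TKA an inclusion criterion, and Recruitment has these patients screened once the operation is booked.

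Withdrawal and Discontinuation says that participants with knee "surgery or a knee injury within the follow-up time or patients who become otherwise severely ill will not be invited for the second visit". Their data already collected are kept. A withdrawn participant is replaced only while enrollment is open, and by someone of the same group type.

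Project Design gives the second visit two uses. The longitudinal dataset tests whether changes in osteoarthritis can be assessed from the biomarkers. A secondary aim is to predict progression as seen at the second visit.

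**The concern.** One of the six groups is defined by a forthcoming knee operation, and a knee operation during follow-up ends eligibility for the second visit. Read literally, the longitudinal dataset cannot contain all 120 participants, and the shortfall is concentrated in the group with severe disease. Project Population includes that group so that the sample covers the range of osteoarthritis stages. Neither the Methods nor the Limitations section mentions the loss. Feature Analysis and Multivariate Modeling relies on n=120 without separating the cross-sectional from the longitudinal dataset.

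The same rule applies in Groups A to C. A participant there who has knee surgery because the osteoarthritis worsened has no second-visit outcome, so the loss may be related to the progression that the secondary aim tries to predict.

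**Working it through.** **Head count**

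- Enrolled: 6 groups × 20 = 120 (Project Population).
- Group D: 20, all booked for TKA (Project Population, Textbox 1).
- Second visit: 9±2 months (Table 1).
- Let q be the share of Group D operated on within follow-up. The article gives no operation dates or waiting times, so q is an assumption.

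Longitudinal N before other losses = 100 + 20 × (1 − q):

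| q | Longitudinal N |
|---|---|
| 1.0 | 100 + 0 = 100 |
| 0.9 | 100 + 2 = 102 |
| 0.75 | 100 + 5 = 105 |

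Surgery, injury, severe illness or withdrawal in Groups A to C lowers each figure. Replacement cannot restore Group D at the second visit, because a Group D replacement is also booked for TKA. The cross-sectional N stays at 120, because first-visit data are kept.

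**The article's own detectable effect**

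Project Population gives a smallest detectable correlation of 0.25 for n=120, 80% power and a significance level of .05. It does not state the sidedness; a two-sided test reproduces the figure. By Fisher's z:

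r = tanh[(1.960 + 0.842) / √(n − 3)]

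- n=120: 2.802 / √117 = 2.802 / 10.817 = 0.259, so r = 0.253. This agrees with the stated 0.25.
- n=100: 2.802 / √97 = 2.802 / 9.849 = 0.2845, so r = 0.277.

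Power for r=0.25, where atanh(0.25) = 0.2554:

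- n=120: Φ(0.2554 × 10.817 − 1.960) = Φ(0.803) = 78.9%.
- n=100: Φ(0.2554 × 9.849 − 1.960) = Φ(0.556) = 71.1%.

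As an illustration of further losses in Groups A to C, n=90 gives r = 0.292 and 66.4% power.

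**Composition in the abstract**

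The abstract counts 100 patients with previous reconstructive surgery. In Project Population, the registry groups B1, B2, C1 and C2 give 4 × 20 = 80. The other 20 are Group D, for whom Textbox 1 requires a booked TKA and not an earlier reconstruction.

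**The case against.** The strongest reply is that little of the study depends on this. It is described as exploratory. Biomarker identification uses the first visit, which was completed for all 120. The withdrawal rule is disclosed, and the prediction of progression is a secondary aim. All of this stands. It limits the consequence but does not reconcile the statements.

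A reader might infer several stronger points that the article does not support:

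- **A fixed ceiling of 100.** This needs every booked operation to take place within follow-up. A postponed or cancelled operation would leave that participant eligible.
- **A failed power statement.** The r=0.25 proxy is given for the full sample and is never claimed for the longitudinal analysis. The figures at n=100 show the size of the loss, and the change in detectable r is modest.
- **First-visit data discarded by the mixed ANOVA.** The text says only "Mixed ANOVA will be used to compare differences in the AE, osteoarthritis grading parameters between groups". It names no within-subject factor. Knee or functional test would fit as well as visit, and the Discussion assigns progression to regression models.
- **A contradiction between Withdrawal and Discontinuation and Handling of Missing Data.** The latter says of missed appointments: "After the second miss, they will be excluded (and replaced if the recruitment phase is still ongoing". This is a general rule tied to replacement. Planned recruitment lasts 6 months and the earliest second visit is at 9 − 2 = 7 months, so it fits first-visit misses. The specific rule for a missed second visit keeps the first-visit data, and the two can be read together.
- **Proven bias toward no effect.** The article gives no rate of, or reasons for, surgery in Groups A to C, so neither the direction nor the size of any bias can be shown.

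It is also fair to say that a replaced joint cannot be graded comparably on Kellgren-Lawrence or MOAKS, and that Project Design ties progression to what is observed at the second visit. Making surgery part of the main definition of progression would therefore change the endpoint.

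**Conclusion.** The point holds for the longitudinal dataset. Two examinations for all 120, a group entered on a booked TKA, and no second visit after knee surgery cannot all stand as written. The expected longitudinal N is about 100 if all Group D operations fall within 9±2 months, and 102 to 105 if 90% to 75% do, before losses in Groups A to C. The cross-sectional dataset of 120 is unaffected. If the article's proxy is applied to 100 participants, the detectable r is about 0.28 and power for r=0.25 is about 71%.

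In Groups A to C, loss through surgery may be related to the outcome. That is reason enough to report it and test sensitivity to it, but it does not establish a bias in a known direction.

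**What to change.** 1. Reconcile the abstract, Project Design and Table 1 with Withdrawal and Discontinuation. State the expected longitudinal N, and whether Group D contributes to it or is cross-sectional only. Once second-visit collection has ended, give the actual number by group.
2. Do not carry n=120 or r=0.25 over to the longitudinal and progression analyses. If a detectable effect is quoted for them, base it on the longitudinal N (about 0.28 at n=100).
3. Report how many participants in Groups A to C had knee surgery during follow-up, and why. Keep progression as observed at the second visit as the main definition, and add a sensitivity analysis that counts surgery for worsening osteoarthritis as progression.
4. Correct the abstract to 80 registry patients with previous knee surgery, 20 patients booked for TKA and 20 healthy controls.

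The cost is wording, a slightly less favourable longitudinal sample size and one extra analysis. No study procedure has to change.
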